#### 2.3.1.3 Exploratory efficacy endpoints

The exploratory efficacy endpoints are:

- Change from baseline in circulating mitochondrial peptides (eg, Mots-C), metabolomics, proteomics; plasma biomarkers of inflammation, adhesion markers, muscle injury (eg, troponins, creatine kinase, fibroblast growth factor-21) biomarkers, and mitochondrial function/metabolism (~1.5 mL total); nitric oxide biology; immune profiling, and metabolism/phenotypic extracellular acidification rate and oxygen consumption rate at Week 4
- The mean change from baseline in energetically active metabolites measured using proton magnetic resonance spectroscopy (1H-MRS; ie, creatine, intramyocellular lipids, acetyl-carnitine, and carnosine) at Week 4
- Change from baseline in predose plasma concentrations of AAs at Week 4 (see Laboratory Manual for details)
- The mean change from baseline in minimal intramuscular pH after exercise, initial PCr recovery rate, adenosine diphosphate (ADP) concentration at the end of exercise, maximal mitochondrial capacity, and other parameters measured using dynamic 31P-MRS at Week 4

### 2.3.2 Efficacy endpoints - Cohort B

- Change from baseline in subjects’ fatigue score as assessed by Chalder Fatigue Questionnaire (CFQ)-11 (by Bimodal Scoring) before a 6MWT at Week 4, and at Day 14 (without 6MWT)
- The proportion of subjects with an improvement in fatigue score as assessed by CFQ-11 before a 6MWT at Week 4
- Change from baseline in distance traveled during a 6MWT at Week 4
- The proportion of subjects with an improvement in distance traveled as assessed by 6MWT at Week 4

### 2.3.3 Safety and tolerability endpoints - Cohort A and B

The safety and tolerability endpoints are:

- AEs and serious adverse events (SAEs)
- Physical examination findings, including vital signs (siting systolic and diastolic blood pressure, heart rate, respiratory rate, body temperature, resting O_2_ saturation) and body weight
- Change in clinical laboratory assessments, including chemistry, hematology, and urinalysis

# 3 STUDY DESIGN

## 3.1 Overall Study Design

###### Cohort A

This is a minimum of one center, randomized, double-blind, placebo-controlled, pilot clinical study in the United Kingdom (Figure 1). The study will evaluate the efficacy and safety of AXA1125 in subjects with fatigue-predominant PASC (>12 weeks after initial infection).

The total study duration for each subject will be approximately 9 weeks. This study will comprise a Screening Period of up to 4 weeks, a Treatment Period of up to 4 weeks, and a Follow-up Period of 1 week.

After obtaining informed consent, subjects will be screened, and approximately 40 eligible subjects

(approximately 20 subjects per arm) will be randomized in a 1:1 ratio to receive BID oral administration of 33.9 g AXA1125 or a placebo. Doses will be self-administered on Days 1 to 28, inclusive. Subjects will have clinic visits on Day 1 and Day 28, as well as telephone visits on Day 14 and 1 week after completion of study product administration. Note: Doses should be self-administered at the clinic visit on Day 1 and Day 28 or End of Treatment (EOT)/Early Termination (ET).

The primary efficacy endpoint is the mean change from baseline at Week 4 in the PCr recovery rate following moderate exercise, as assessed by 31P-MRS, which will be evaluated at Screening and EOT/ET (Visit 4). Additional endpoints for assessment of muscle function, safety, tolerability, and exploratory efficacy endpoints will be assessed during the study

Details of randomization will be provided in the Randomization Plan and Interactive Response Technology (IRT) system.

Figure 1 Study Schematic - Cohort A

[figure not shown]

BID=twice daily; D=Day; MRS=magnetic resonance spectroscopy; PRO=patient-reported outcomes.

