###### Cohort B

An additional cohort (approximately 10 subjects) will be added to the study which will include subjects who were considered screen-failures for Cohort A due to their PCr recovery rate constant (< 50 seconds) provided their CFQ-11 Total Score is _≥_8 and meet the rest of the eligibility criteria.

The total study duration for each subject in Cohort B will be approximately 6 weeks, which will comprise a Screening Visit (1 week), Baseline Visit, a Treatment Period of 4 weeks, and a Follow-up Period of 1 week.

After obtaining informed consent, subjects will be re-screened and approximately 10 eligible subjects will be randomized in a 1:1 ratio (double-blind, placebo-controlled) to receive either twice daily (BID) oral administration of 33.9 g AXA1125 or a placebo.

Doses will be self-administered on Days 1 to 28, inclusive. Subjects will have clinic visits on Days 1, and 28, as well as telephone visits on Day 14, and 1 week after completion of study product administration.

The efficacy endpoints for Cohort B include the change from baseline at Week 4 in subjects’ fatigue score, as assessed by Chalder Fatigue Questionnaire (CFQ)-11 (by Bimodal Scoring) before 6 MWT, which will be evaluated at Screening, Baseline, and End of Treatment or Early Termination. CFQ-11 will also be assessed at Day 14 (without 6MWT). Additional endpoints for assessment of functional status, safety, and tolerability will be assessed. Details of randomization will be provided in the Randomization Plan and Interactive Response Technology (IRT) system.

Figure 2 Study Schematic - Cohort B

[figure not shown]

BID=twice daily; D=Day; PRO=patient-reported outcomes.

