## 3.4 Study Duration

**Cohort A**

Subjects will participate for up to 9 weeks. The study will comprise a Screening Period of up to 4 weeks, a Treatment Period of 4 weeks, and a Follow-up Period of 1 week. **Cohort B**

The total study duration for each subject in Cohort B will be approximately 6 weeks, which will comprise a Screening Period (1 week), Baseline Visit, a Treatment Period of 4 weeks, and a Followup Period of 1 week.

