### 4.5.3 Handling of discontinuation of study drug and study withdrawals

If the PI discontinues a subject from study drug due to development of an AE, every effort should be made to complete the ET procedures as outlined in the Schedule of Assessments (SOA;

APPENDIX 1; APPENDIX 2) as soon as possible after the last dose of study drug and to monitor the subject for resolution of the AE or for the development of new AEs for 4 weeks after the last dose of study drug.

If a subject withdraws consent or is terminated for any other reason, every effort should be made to complete the ET assessments as outlined in the SOA (APPENDIX 1; APPENDIX 2).

The reason for subject withdrawal must be documented in the eCRF.

Subjects who discontinue or withdraw from the study will not be replaced.

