## 6.7 Collection and Reporting of Adverse Events

AEs including SAEs will be monitored by nonleading questions posed to subjects at each study visit. AEs will be graded by seriousness, severity, and relationship to the study drug for the duration of the study. The PI or delegate will routinely review laboratory results for any clinically significant abnormal results that may represent potential AEs and document any findings in the source documents.

In the event that any subject experience an AE that is considered by the PI to be possibly, probably, or definitely related to study drug and that is severe or medically significant, that subject should be discontinued from further study drug administration and monitored for resolution of the event. Study drug should be discontinued regardless of other factors such as threat to life or admission to hospital.

In the event that 3 subjects experience the same AE meeting the criteria described above or when 2 subjects experience the same AE that is life-threatening or requires immediate intervention to prevent death and that is attributed to study drug, enrollment in the study should be temporarily halted to allow further evaluation.

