### 6.7.4 Reporting of adverse event and serious adverse event

#### 6.7.4.1 Adverse event

AEs, which include clinical laboratory test results, will be monitored and documented from the time of informed consent until following the last administration of study drug through the Follow-up Period (Day 35). Subjects should be instructed to report any AE that they experience to the PI, whether or not they think the event is due to study drug. The PIs should make an assessment for each AE at each visit and record the event on the appropriate AE eCRF. Each AE should be followed until it resolves or until the end of the Follow-up Period.

Wherever possible, a specific disease or syndrome rather than individual-associated signs and symptoms should be identified by the PI and recorded on the eCRF. However, if an observed or reported sign or symptom is not considered a component of a specific disease or syndrome by the PI, it should be recorded as a separate AE on the eCRF. Additionally, the condition that led to a medical or surgical procedure (eg, surgery, endoscopy, tooth extraction, or transfusion) should be recorded as an AE, not the procedure itself.

Any medical condition already present at the Screening Visit should be recorded as medical history and not be reported as an AE unless the medical condition or signs or symptoms present at Baseline changes in severity, frequency, or seriousness at any time during the study. In this case, it should be reported as an AE.

Clinically significant abnormal laboratory or other examination (eg, echocardiogram) findings that are detected during the study or are present at the Screening Visit and significantly worsen during the study should be reported as AEs, as described below. The PI will exercise their medical and scientific judgement in deciding whether an abnormal laboratory finding or other abnormal assessment is clinically significant. Clinically significant abnormal laboratory values occurring during the clinical study will be followed until follow-up tests return to normal, stabilize, or are no longer clinically significant. Abnormal test results that are determined to be an error should not be reported as an AE. Laboratory abnormalities or other abnormal clinical findings (eg, echocardiogram abnormalities) should be reported as an AE if any of the following are applicable:

- If an intervention is required as a result of the abnormality;

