#### 6.7.4.2 Serious adverse event

Collection of SAEs will only be up to 7 days following the last dose, however, follow-up on ongoing SAEs will continue until resolution or 4 weeks following the administration of the last dose of the study drug. After the 7 days reporting window, any SAE that the PI considers related to the study drug must be reported to Medpace Clinical Safety and the Sponsor/designee.

To report the SAE, complete the SAE form electronically in the eCRF. When the form is completed, Medpace Safety personnel will be notified electronically and will retrieve the form. If the event meets serious criteria and it is not possible to access the eCRF, send an email to Medpace Safety at **[contact]** or call the Medpace SAE hotline (phone number listed below) and fax/email the completed paper SAE form to Medpace (contact information listed below) within 24 hours of awareness. When the eCRF becomes available, the SAE information must be entered within 24 hours of the system becoming available.

The PI must continue to follow up the subject until the SAE has subsided or until the condition becomes chronic in nature or stabilizes (in the case of persistent impairment) or the subject dies.

Within 24 hours of receipt of follow-up information, the PI must update the SAE form electronically in the eCRF and submit any supporting documentation (eg, subject discharge summary or autopsy reports) to Medpace Clinical Safety via fax or email. If it is not possible to access the eCRF, refer to the procedures outlined above for initial reporting of SAEs.

Safety contact information Medpace Clinical Safety

Medpace SAE hotline – USA:

[contact], dial “3” or [contact], dial “3”

[contact] or [contact]

Email: [contact]

Medpace SAE hotline – Europe:

[contact]

[contact]

Email: [contact].

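### The ±3-day window on Visit 5 lets the final safety call fall 4 to 6 days after a Day 28 last dose, so the last 1 to 3 days of AE and SAE collection can pass without a scheduled question (minor)

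*Protocol*

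**What the plan says.** Protocol 3.1 has subjects dose themselves on Days 1 to 28 in both cohorts. For Cohort A it plans "telephone visits on Day 14 and 1 week after completion of study product administration", and for Cohort B "telephone visits on Day 14, and 1 week after completion of study product administration". Section 3.4 describes "a Treatment Period of 4 weeks, and a Follow-up Period of 1 week" for Cohort A, and the same lengths for Cohort B. Both schedules (Appendices 1 and 2) place Visit 5, by telephone, on Day 35 with a window of ±3 days.

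The safety sections set the collection periods:
- Section 6.7: "AEs including SAEs will be monitored by nonleading questions posed to subjects at each study visit".
- Section 6.7.4.1: AEs are documented from consent through the Follow-up Period, whose end is given as Day 35. It adds: "Subjects should be instructed to report any AE that they experience to the PI".
- Section 6.7.4.2: "Collection of SAEs will only be up to 7 days following the last dose". SAEs that the investigator considers related remain reportable after that.
- Section 4.5.3: a subject taken off drug for an AE is watched "for the development of new AEs for 4 weeks after the last dose of study drug".

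No contact is scheduled after Visit 5.

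**The concern.** The target day for Visit 5 is right, but its window allows the call before the period it is meant to cover has ended. Visit 5 is the only scheduled contact between the end-of-treatment visit and the end of the study for a completer. It is therefore the one occasion on which a post-treatment event is actively asked about. If the call is made early, events in the remaining days depend on the subject reporting them unprompted.

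Safety and tolerability is a secondary objective in Cohort A (2.1.2) and one of only two objectives in Cohort B (2.2). The sponsor has itself linked the SAE window to scheduled contacts: the rationale in Appendix 5 for shortening it to 7 days is that no visit is scheduled 4 weeks after the last dose. A 7-day window that a compliant final call need not reach fits poorly with that reasoning.

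The case at stake is narrow: a completer who is called on Days 32 to 34, has a new event in the days that remain, and does not report it. Efficacy is not touched, and the window is the same in both arms.

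**Working it through.** **Inputs**
- Last planned dose: Day 28 (3.1, both cohorts).
- Visit 5: Day 35, window ±3 days (Appendices 1 and 2).
- End of SAE collection: last dose + 7 days (6.7.4.2).
- End of AE collection: Day 35 (6.7.4.1).
- Scheduled questioning: at each study visit (6.7); Visit 5 is the last.

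**The protocol's own figure.** 28 + 7 = Day 35. Text and schedules agree on the target day, and for a Day 28 last dose the AE and SAE windows end together.

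**Effect of the window.** Permitted call days are 35 − 3 to 35 + 3, that is Days 32 to 38 (7 days). Interval since last dose = call day − 28. Days without a scheduled question = max(0, 35 − call day).

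| Call day | Days since last dose | Days without a scheduled question |
| --- | --- | --- |
| 32 | 4 | 3 |
| 33 | 5 | 2 |
| 34 | 6 | 1 |
| 35 | 7 | 0 |
| 36 | 8 | 0 |
| 37 | 9 | 0 |
| 38 | 10 | 0 |

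Three of the 7 permitted days leave a gap. The largest gap, from a Day 32 call, is 3/7 = 43% of the post-treatment week, or 3/35 = 8.6% of Days 1 to 35. If all seven days were equally likely, which is an assumption, the mean gap would be (3 + 2 + 1)/7 = 0.86 day per completer. The share of subjects called early is not given and could be anything from none to all.

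**Dependence on the last dose day.** Visit 4 also has a ±3-day window, and 3.1 notes that a dose should be taken at the clinic visit on Day 28 or at EOT/ET.
- Last dose Day 31: the SAE window ends on Day 38. A Day 32 call comes 1 day after dosing and leaves 38 − 32 = 6 days of it. This requires the visit note to override dosing on Days 1 to 28, so the finding does not rest on it.
- Last dose Day 25: the SAE window ends on Day 32 and every permitted call covers it. Calls on Days 32 to 34 still fall 3, 2 or 1 days short of the Day 35 end of AE collection.

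**After the change.** First permitted day = max(35, last dose + 7); window 0/+3. AE collection ends at max(35, last dose + 7).

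| Last dose | First permitted day | Call days | Days since last dose | Uncovered days |
| --- | --- | --- | --- | --- |
| Day 28 | max(35, 35) = 35 | 35–38 | 7–10 | 0 |
| Day 31 | max(35, 38) = 38 | 38–41 | 7–10 | 0 |
| Day 25 | max(35, 32) = 35 | 35–38 | 10–13 | 0 |
| Day 10 (stops drug, stays in study) | max(35, 17) = 35 | 35–38 | 25–28 | 0 |

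**The case against.** The strongest answer is that nothing here is misstated. Any tolerance around a target day allows days before it, a ±3-day window is common, and Visits 3 and 4 have the same one. Collection is fixed by date or by the last dose and not by the call. Subjects are told to report any AE, related SAEs stay reportable, and those stopped for an AE are monitored for 4 weeks. Little new post-treatment risk is visible: fasted amino acid levels showed no accumulation (1.5.2.2). In the 16-week NAFLD study, selected gastrointestinal events had median onsets of 12.5 to 25.5 days after starting drug (1.5.2.1).

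Most of this stands, and it is why the point is minor. It does not remove the point. The safeguards either rely on unprompted reporting or apply to subjects other than completers, so none restores the question that an early call omits.

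A reader might infer more: that events on the last days go uncollected, or that follow-up formally ends at the early call. The documents do not support this, because 6.7.4.1 and 6.7.4.2 keep collection open whatever the call date. Nor do the design text and the schedules contradict each other on the target day.

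A further objection concerns the remedy. It is tempting to tie both Visit 5 and the end of AE collection simply to 7 days after the last dose, but that would harm subjects who stop drug and remain in the study under 4.5.2. For a subject stopping on Day 10, AE collection would end on Day 17 instead of Day 35, a loss of 35 − 17 = 18 days. Visit 5 would fall on Days 17 to 20, before Visit 4 on Day 28. After an AE, the Day 17 end would also clash with the 4 weeks of monitoring in 4.5.3, which run to Day 38. This objection is correct, and the remedy has to avoid that outcome.

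**Conclusion.** The point holds as a minor weakness in scheduling, in both cohorts. With a last dose on Day 28, 3 of the 7 permitted Visit 5 days come before the 7-day SAE window and the Day 35 AE window have ended, and they leave 1 to 3 days without a scheduled safety question. What is lost is active questioning, not collection.

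The 1-to-3-day figure assumes a Day 28 last dose and no contact after Visit 5. The 3-day maximum is not a general bound, since a dose taken at a late Visit 4 would widen the gap in the SAE window. How many subjects would be called early is unknown, and no lost event can be shown. The matter is best treated as a cheap improvement.

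**What to change.** - **Appendices 1 and 2:** replace the ±3-day window for Visit 5 with 0/+3 days, starting at the later of Day 35 and 7 days after the last dose.
- **Section 6.7.4.1:** state the end of AE collection as the later of Day 35 and 7 days after the last dose. Day 35 stays as the minimum and should not be replaced by the last-dose rule alone.
- **Sections 4.5.2, 4.5.3 and 6.7.4.2:** no change. Subjects who stop drug early keep AE collection to Day 35, their Visit 4 and, after an AE, the 4 weeks of monitoring.

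The cost is one cell and a footnote in each schedule and one phrase in 6.7.4.1. Operationally, the site has 4 permitted days for a telephone call instead of 7, and some calls move a few days later. For a Day 28 last dose the latest permitted day remains Day 38.

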###### Cohort B

An additional cohort (approximately 10 subjects) will be added to the study which will include subjects who were considered screen-failures for Cohort A due to their PCr recovery rate constant (< 50 seconds) provided their CFQ-11 Total Score is _≥_8 and meet the rest of the eligibility criteria.

The total study duration for each subject in Cohort B will be approximately 6 weeks, which will comprise a Screening Visit (1 week), Baseline Visit, a Treatment Period of 4 weeks, and a Follow-up Period of 1 week.

After obtaining informed consent, subjects will be re-screened and approximately 10 eligible subjects will be randomized in a 1:1 ratio (double-blind, placebo-controlled) to receive either twice daily (BID) oral administration of 33.9 g AXA1125 or a placebo.

Doses will be self-administered on Days 1 to 28, inclusive. Subjects will have clinic visits on Days 1, and 28, as well as telephone visits on Day 14, and 1 week after completion of study product administration.

The efficacy endpoints for Cohort B include the change from baseline at Week 4 in subjects’ fatigue score, as assessed by Chalder Fatigue Questionnaire (CFQ)-11 (by Bimodal Scoring) before 6 MWT, which will be evaluated at Screening, Baseline, and End of Treatment or Early Termination. CFQ-11 will also be assessed at Day 14 (without 6MWT). Additional endpoints for assessment of functional status, safety, and tolerability will be assessed. Details of randomization will be provided in the Randomization Plan and Interactive Response Technology (IRT) system.

Figure 2 Study Schematic - Cohort B

[figure not shown]

BID=twice daily; D=Day; PRO=patient-reported outcomes.

## 3.2 Scientific Rationale for Study Design

**Cohort A**

This pilot study is designed to assess AXA1125 dosed for up to 4 weeks in subjects with PASC. The primary objective is to assess the impact AXA1125 on muscle function (metabolism) following exercise. Key secondary objectives include assessment of the relationship between AXA1125 and functional status and assessment of the safety and tolerability of AXA1125 in subjects with PASC. It is anticipated that the administration of AXA1125 for up to 4 weeks in subjects with PASC will have an impact on muscle bioenergetics and consequently muscle function. 31P-MRS, 6MWT, and CFQ-11 are utilized as appropriate scales for the assessment of the study endpoints. Accordingly, the mean change from baseline at Week 4 in PCr recovery rate following moderate exercise, as assessed by 31P-MRS, was chosen as the primary endpoint for the study. With relatively rapid time resolution (<8 seconds) and certain assumptions, a range of bioenergetic refluxes will be determined from the metabolic changes. In particular, a functional estimate of mitochondrial oxidative capacity can be calculated from the kinetics of PCr recovery.

Additional biomarkers will be evaluated as exploratory endpoints to provide additional information about the full mechanism of action of AXA1125 and to assist in the design of the future development program.

A sample size of approximately 40 subjects (20 subjects per arm) will be enrolled in the study. In order to detect a meaningful treatment difference of 10 second improvement, approximately 32 subjects will provide 80% power at a 2-sided, 5% significance level, in addition to approximately 20% dropout rate.

This sample size will also allow for a general assessment of safety and tolerability of AXA1125 in this population. **Cohort B**

This Cohort is designed to assess AXA1125 dosed for up to 4 weeks in approximately 10 additional subjects with PASC, including subjects who were considered screen-failures due to their PCr recovery rate constant (< 50 seconds), provided their CFQ-11 score is ≥8 and they meet all the eligibility criteria for the study.

The key objectives for Cohort B include assessment of the relationship between AXA1125 and functional status, and assessment of safety and tolerability of AXA1125 in subjects with PASC.

Additionally, this Cohort is anticipated to provide valuable information on understanding the relationship between Baseline PCr and CFQ-11 results and AXA1125 responses.

CFQ-11, and 6MWT are utilized as appropriate scales for the assessments of this cohort’s endpoints. As an interim look at the data from Cohort A indicated that there was a statistically significant improvement in Fatigue using CFQ-11 when assessed prior to 6MWT.

A sample size of approximately 10 subjects will be enrolled, randomized in a 1:1 ratio to receive either twice daily (BID) oral administration of 33.9 g AXA1125 or a placebo.

This sample size will also allow for a general assessment of safety and tolerability of AXA1125 in this population.

